## Abstract

**Background:**

Bipolar disorders are serious illnesses with a chronic course and a high rate of relapse. Typically, bipolar disorders onset during adolescence or early adulthood, with patients experiencing significant personal and social costs as a consequence of their illness. Despite this, to date, there is limited (controlled) evidence regarding the effectiveness of psychotherapy during the critical stages of the disorder (e.g., early onset). Some preliminary studies suggest that targeted, tailored early interventions in particular may improve disease prognosis. The proposed study examines the effectiveness of group psychotherapy on relapse prevention, global adaptive functioning, and neuropsychological functioning in early-stage bipolar disorder.

**Methods:**

In this multicenter randomized controlled trial (RCT), 300 patients with bipolar disorder are randomized to one of two group psychotherapies: Specific Emotional-Cognitive Therapy (SECT; intervention group) or Emotion-Focused Supportive Therapy (EFST; active control group). Each therapy comprises of a total of 48-h sessions (delivered once a month) over a period of 4 months. Assessments take place at baseline (t1); 6 months follow-up, i.e., post-intervention (t2); 12 months follow-up (t3); and 18 months follow-up (t4), whereby 18 months follow-up is the primary time point of interest.

**Discussion:**

The goal of this study is to test the effects of an innovative, specific group therapy relative to an active control condition in terms of rates of relapse, global functioning, and neuropsychological functioning. Pending the outcomes of the trial, it will be possible to establish a firm evidence base for accessible group psychotherapy adjuvant to routine psychiatric care for individuals with bipolar disorder.

**Trial registration:**

USA: ClinicalTrials.gov NCT02506322. Registered on 19 December 2014; Germany: German Clinical Trials Register DRKS00006013. Registered on21 May 2015

## Background

Bipolar disorders are serious illnesses with a chronic course and a high rate of relapse. Compared to unipolar major depressive episodes, patients suffering from bipolar disorder have more than twice as many new episodes (relapses) despite psychiatric care and mood-stabilizing medication. Although the classical description by Kraepelin implies a recurrent disorder with full inter-episodic remission, modern epidemiologic and neuropsychological research has revealed long-term deficits in psychosocial well-being, quality of life, and cognitive functioning [1]. The onset age of bipolar disorders is typically during late adolescence and early adulthood. This is a very sensitive phase for educational, professional, and social development. In addition, this is a critical time in the developmental lifespan characterized by the establishment of one’s personality and often experimentation with oppositional attitudes, chaotic social and sleeping rhythms, and drug use. In bipolar disorder, such activities may challenge compliance and increase the risk of relapse. In particular, young adults (< 30 years) in the early stage of illness experience the highest illness burden with considerable personal costs (e.g., socially, professionally, and personally) and are most vulnerable to death by suicide. Recent meta-analyses of available clinical trials [2, 3] conclude (a) a limited availability of psychotherapy studies in bipolar disorder patients in general and (b) no existing studies focusing on specific subgroups of patients (e.g., early course of disorder and first onset cases). Recently, a staging model implying that bipolar disorder can be classified as a chronic, recurrent disease has been proposed and entails the following stages: asymptomatic (stage 0), prodromal with a low to high-risk profile (stage 1a/1b), onset (stage 2), early stage with occasional relapses and long inter-episode remission periods (stage 3a/b), multiple relapses (3c), and refractory therapeutic course with persistent symptoms and functional deficits (stage 4 [4];).

Applying this model to patients enrolled in psychotherapy studies has shown that the average duration of illness and the number of episodes (on average > 20 episodes) of the examined samples must be assumed to be of stage 3a–c. At the same time, retrospective analyses repeatedly showed that patients of younger age and with few episodes (stages 2–3a) showed significantly better effects of psychotherapeutic interventions [3]. Besides several other RCTs in bipolar depressed patients, we [5] have conducted a RCT with bipolar disorder patients, showing that individual cognitive behavioral therapy (CBT) is superior to individual supportive intervention [6].

Considerations on the stages model of bipolar disorder have therefore also influenced the conceptualization of psychotherapy interventions in recent years: Firstly, two studies examined whether the transition to bipolar disorder could be prevented in the prodromal phase for high-risk individuals [7, 8]. Concerning the late stages of the disease, psychotherapeutic manuals have been developed, specifically targeting functional and cognitive deficits in order to counteract progressive chronicity and functional deficits [9–13]. Within the early stages of the initial disease onset, a number of interventions have been assessed; however, mostly they investigate the influence of psychotherapy on the early course of bipolar disorders with the lack of a control group and with small numbers of cases or without active control conditions (for a review, see [14]. This prompted us to consider the question as to what extent a specific, cognitive behavioral therapy could be superior to a supportive, experience- and emotion-focused intervention in young bipolar patients within the early stage of their disease.

## Methods

### Aims and hypotheses

The general aim of this study is to improve the evidence for psychotherapeutic interventions in relapse prevention for bipolar patients. In order to do so, we wanted to compare two different treatment approaches, to implement new treatment manuals into standard treatment (as there is so far only one available in Germany) and to target patients that are not accessed by the existing practices. Finally, it is our aim to identify clinical and neurobiological predictors for response to psychotherapeutic interventions in bipolar disorder.

To approach these aims, we wanted to test three groups of hypotheses regarding the addition of a specific, innovative psychotherapy (SECT) to psychiatric care in young bipolar patients in the early stage of their disease. Our outcomes are defined as follows: primary—(1) reduced rate of relapse (development of a new affective episode); secondary—(2) reduced missed days at work/school, days spent in hospitals, and health costs; improved medical treatment compliance and social functioning; (3) normalized neurobiological functioning; pre-treatment neural alterations in neurobiological systems will predict post-treatment outcome of SECT, with the greatest improvement in SECT for patients with the most pronounced neural alterations prior to treatment.

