### Sample size calculation

Sample size calculations refer to a log-rank statistic under *α* = 0.05 and *β* = 0.2 (80% power) under the assumptions of (a) an accrual time of 24 months, (b) a total study duration of 48 months with a primary time point of interest at 18 months post-baseline, and (c) a drop-out rate of 12% (the latter based on experiences from previous studies [2, 3, 5]; and relates to the study observation period of 18 months). We define a treatment effect of factor 2 as a relevant effect, i.e., a hazard ratio (HR) of 0.5, for instance, is regarded as a relevant effect. Previous trials have indicated about 4% of the study population under risk (excluding dropouts) will experience a relapse under conventional therapy each month. HR = 0.5 would require 2% per month for the SECT group and a study population of *N* = 360 patients (180 patients per treatment arm) to reach significance under *α* = 0.05 and *β* = 0.2. The study with a proposed *N* = 300 would require HR = 0.46, and the pessimistic scenario of *N* = 200 would have to reach HR = 0.375. Thus, the study with *N* = 300 intended can yield statistical significance if the treatment effect in the SECT group exceeds factor 2. In addition, our sample size calculation is based on the publication by Jahn-Eimermacher et al. [33] which fits—regarding sample sizes for time-to-event data—the requirements of the present study best and results in an identical sample size.

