### Statistical analysis

The question as to whether specific psychotherapy can prolong the time until relapse will be addressed by non-parametric survival analyses involving log-rank or Wilcoxon statistics and sensitivity analyses for the ITT (intent-to-treat) sample and the PP (per-protocol, required is participating in at least 75% of treatment sessions) sample. The time-dependent evolution of group-specific hazard rates will be investigated by parametric models addressing the differences in the dynamics of relapse in both intervention arms. Cox regressions will be performed to identify the risk factors for the probability of relapse and time until relapse if the proportional hazard assumption will not be negated. Our planned analyses will allow to identify if the types of participants with missing outcomes look different to those observed outcomes and whether this pattern might be different by arm: treatment arm with no missing primary outcome at primary time point, treatment arm with missing primary outcome at primary time point, control arm with no missing primary outcome at primary time point, and control arm with missing primary outcome at primary time point. Secondary endpoints like symptomatology, days missed at work/school, or social functioning level will be described on a univariate level and enter multivariable group comparisons on the base of an ANCOVA (with the factor kind of intervention (2) and time points (2 to 4) using baseline as a covariate) and involve stepwise variable selection. Based on the results for these covariates, methods such as principal component analysis or latent variable modeling will finally be considered to identify the risk factors for the probability of relapse and time until relapse. We have the intention to use the CONSORT statement for reporting the outcome and final results of this randomized controlled trial.

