One strength of our study lies in the profound experience of the authors in planning and implementing multicenter RCTs in psychotherapy with an emphasis on affective disorders. The second strength is the fact that the study is embedded in the “Network for the Research in Psychiatric Diseases” funded by the Federal Ministry for Education and Research (BMBF). This network merged the most active academic centers for bipolar disorder research in Germany with significant funding to address the research agenda. For instance, a unique electronic study platform has been established for this project. This platform has since enabled the network to improve and simplify data collection and management over the study centers which are distributed nationwide in Germany.

This accumulation of expertise and great logistical support enables us to conduct the biggest RCT in the field of psychotherapy in bipolar disorders to date. On the basis that the study is conducted across multiple sites, we have managed to recruit a large sample size and to create a setting that enables the inclusion of patients from both urban and more difficult-to-reach rural areas. With recruitment of 300 bipolar patients in remission, we are in a position to examine a wide range of scientific questions beyond our primary hypothesis, especially the search for clinical and neurobiological (fMRI) predictors for psychotherapeutic success.

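### The neural predictor hypothesis is worded within the SECT arm, so as written it could not separate a predictor of response to SECT from a prognostic marker or regression to the mean

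*Protocol article*

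**What the plan says.** The protocol article's section Aims and hypotheses sets a general aim: "it is our aim to identify clinical and neurobiological predictors for response to psychotherapeutic interventions in bipolar disorder". The third group of hypotheses then has two parts. One is that neurobiological functioning normalises. The other, the predictor clause, is that "pre-treatment neural alterations in neurobiological systems will predict post-treatment outcome of SECT". The direction is fixed as well: the article expects this "with the greatest improvement in SECT for patients with the most pronounced neural alterations prior to treatment". The clause does not mention EFST.

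The section Primary and secondary outcome measures lists improved neurobiological functioning among the outcomes on which SECT is compared with EFST. The first part of hypothesis 3 is therefore an arm contrast.

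In Statistical analysis, "Cox regressions will be performed to identify the risk factors for the probability of relapse and time until relapse", provided that proportional hazards is not rejected. Later, "methods such as principal component analysis or latent variable modeling will finally be considered to identify the risk factors for the probability of relapse". Secondary endpoints go into an ANCOVA "with the factor kind of intervention (2) and time points (2 to 4) using baseline as a covariate". These analyses and the log-rank test compare the arms, but no named term lets the arm difference vary with a marker, and no model is assigned to the predictor clause.

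The Discussion returns to the aim, "especially the search for clinical and neurobiological (fMRI) predictors for psychotherapeutic success".

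**The concern.** A predictor of response to SECT is a marker across whose levels the SECT-EFST difference changes. A marker associated with outcome among SECT patients, or with relapse in both arms pooled, need not have that property. It may simply forecast the course of illness, and do so equally under EFST.

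Where improvement is measured as change on the neural measure itself, there is a second problem. Patients with the most abnormal first reading tend to have a less abnormal second one, with or without an effective treatment. That pushes in exactly the direction the clause predicts.

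At stake is the interpretation of a secondary aim that the Discussion gives some prominence. A positive finding could be read as guidance on whom to offer SECT when it carries no such information. The primary relapse comparison is untouched.

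**Working it through.** The plan gives no figure for the predictor clause, so there is none to reproduce. The check takes its setting from the section Sample size calculation and adds assumptions, marked as such.

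**Inputs from the protocol article:** N = 300, taken as 150 per arm; relapse 4% per month in the control arm; hazard ratio 0.46 for N = 300, so 0.04 × 0.46 = 1.84% per month under SECT; dropout 12% over 18 months. Whether the stated N follows from these rates is a separate question and does not enter here.

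**Assumptions:** prognostic hazard ratio 1.3 or 1.5 per SD of the marker; retest correlation ρ of the neural measure 0.5 to 0.9; 150 or 30 patients per arm with neural data; two-sided 5% tests.

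**1. Expected relapses.** Dropout hazard = −ln(0.88)/18 = 0.0071 per month.
- EFST: 0.04/0.0471 × (1 − exp(−0.0471 × 18)) = 0.485, times 150 = 73.
- SECT: 0.0184/0.0255 × (1 − exp(−0.0255 × 18)) = 0.266, times 150 = 40.
- Total: about 113.

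**2. Relapse, marker purely prognostic.** Share of simulated trials with a significant result, in either direction:

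| Marker hazard ratio per SD | SECT-only Cox | Pooled Cox main effect | Treatment-by-marker interaction |
|---|---|---|---|
| 1.0 | 7% | 6% | 6% |
| 1.3 | 40% | 79% | 5% |
| 1.5 | 74% | 99% | 6% |

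Only the interaction stays near its nominal level when there is no effect modification.

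**3. Relapse, marker a true modifier.** The error can also go the other way. With a prognostic hazard ratio of 1.3 and an interaction of 0.7 per SD, the net hazard ratio within SECT is 1.3 × 0.7 = 0.91. The SECT-only model then detects it in 8% of trials and the interaction in 44%. With an interaction of 0.5, the pooled main effect is significant in 4% of trials and the interaction in 96%.

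**4. Change on the same neural measure, no treatment effect.** With equal variances at both times, the correlation of improvement with baseline is (1 − ρ)/√(2(1 − ρ)) = √((1 − ρ)/2).

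| ρ | Correlation | Significant, 150 SECT patients | Significant, 30 SECT patients |
|---|---|---|---|
| 0.5 | 0.50 | 100% | 84% |
| 0.7 | 0.39 | 100% | 58% |
| 0.8 | 0.32 | 98% | 42% |
| 0.9 | 0.22 | 78% | 21% |

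The arm-by-baseline interaction was significant in 4% to 6% throughout. As an illustration of size, the most abnormal quarter of a normal marker lies on average 1.27 SD from the mean. Its apparent improvement is (1 − ρ) × 1.27, which is 0.64 SD at ρ = 0.5 and 0.25 SD at ρ = 0.8. The plan defines no such quarter.

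**5. Precision of the interaction.** SE = √(1/73 + 1/40) = 0.197 per SD. At 80% power the detectable ratio of hazard ratios is exp(2.80 × 0.197) = 1.7 per SD, or about 0.58 in the protective direction. For an interaction of 0.7 per SD, simulated power is 43% to 44%. These figures suppose that all 300 patients have the marker; fewer scanned patients would weaken them.

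**The case against.** The strongest reply is that this is an omitted model term for an exploratory hypothesis, which an article may leave to the full protocol or analysis plan. Nothing in Statistical analysis excludes an interaction. That stands as far as the model goes. It does not cover the hypothesis, whose wording is in the article and could be satisfied from SECT data alone. An analysis plan that followed it faithfully would inherit the problem.

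Three stronger readings are tempting, and the article does not support them.

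- *The trial will report prognostic factors as predictors of response to SECT.* No model is assigned to the neural clause. The Cox and latent-variable analyses are described as a search for risk factors, which is already prognostic language, and the general aim speaks of psychotherapeutic interventions in the plural.
- *Regression to the mean undermines the neurobiological outcome.* The outcomes section makes that outcome a comparison of SECT with EFST. Randomised arms regress alike, so the effect cancels in the contrast.
- *The EFST arm goes unused.* The survival comparison and the ANCOVA both use it; what is missing is a comparison of arms by marker level.

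Two further limits stand. Improvement is not defined, and regression to the mean does not arise for time to relapse. For relapse, a marker of worse prognosis would run against the hypothesised direction: it would hide effect modification rather than mimic it. The percentages in step 2 therefore show that association within SECT is uninformative about modification; they are not rates at which the clause would be confirmed in its stated direction.

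**Conclusion.** The point holds for the predictor clause of hypothesis 3 and for the factor-finding models, and no further. As worded, they could not distinguish a predictor of response to SECT from a prognostic marker or, where improvement is change on the same neural measure, from regression to the mean.

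Without effect modification, SECT-only tests were significant in 40% to 74% of trials for the assumed prognostic markers, and in 21% to 100% for change on baseline across the assumed retest correlations and sample sizes. The interaction stayed at about 4% to 6%. The sizes depend on those assumptions; the failure to distinguish does not. The matter is minor, because the aim is secondary and the remedy is mostly a change of wording.

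**What to change.** - Restate the clause as a moderator hypothesis: the SECT-EFST difference increases with baseline neural alteration.
- Test it in both arms together with a treatment-by-marker interaction, keeping the marker continuous: a Cox model for relapse, a baseline-adjusted ANCOVA for continuous outcomes. Where the outcome is the neural measure itself, the term is arm by baseline.
- Define the outcome in which improvement is judged.
- Label the result exploratory, since interaction power is limited and the number scanned is not stated. Interpret main-effect Cox results as prognostic only.

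The cost is a reworded hypothesis and one model term. No new data should be needed: the planned SECT-versus-EFST comparison of neurobiological functioning implies neural measurements in both arms. Table 1 does not list them, so the sponsor should confirm this. The price is an imprecise estimate.

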### Design and procedure

This psychotherapy study is designed as a parallel-group, individually randomized controlled trial (RCT) with blind assessment raters. Patients are screened at baseline (t1) by trained diagnostic clinicians (clinical psychologists or psychiatrists) and enrolled giving their informed consent to the study protocol and meeting full inclusion criteria. Patients are then individually randomized to one of the respective treatment groups. Patients will be immediately informed via phone call about the randomization result by the group therapist they are located to. The group therapist will invite the patient to the next possible group meeting. Groups are ongoing, slow-open groups, admitting new participants when someone is terminated. The intervention takes place over up to 5 months between t1 and t2 and is delivered in four full therapy days of approximately 8 h in small groups up to eight subjects. Patients are then seen at the end of treatment (t2 at month 6) and twice during follow-up (t3 at month 12; t4 at month 18). The flowchart (see Fig. 1) visualizes the study steps.

**Fig. 1 Fig1:**
[figure not shown]
Flowchart summarizing the contact occasions with participants over the course of the study. Notes: *SECT = specific Emotional-Cognitive Therapy for relapse prevention in bipolar disorders (German term: **S**pezifische, **E**motional-**K**ognitive **T**herapie). **EFST = Emotion-Focused Supportive Therapy for relapse prevention in bipolar disorders (German term: **F**ördernde, **E**motionsfokussierte, **S**upportive **T**herapie)

### Setting and participants

Participants are recruited at 10 university hospital settings providing both in- and outpatient care for individuals with affective disorders within Germany (Eberhard Karls University Tübingen; Charité University Medicine, Berlin; Medical School Brandenburg Theodor Fontane, Neuruppin; University Hospital Carl Gustav Carus Dresden; Ruhr University Hospital Bochum; University Medical Center Hamburg-Eppendorf; University Medical Centre Göttingen; Philipps University Medicine, Marburg; Ludwig Maximilians University Medicine, Munich; Johann-Wolfgang von Goethe University Medicine, Frankfurt). In addition, we will organize local presentations for the public about bipolar disorder, use local media and the clinic homepage to provide information about the study, and use national organization (DGBS) to inform members and their local self-help groups. First, participants are preliminarily telephone screened by a member of the study team to confirm the eligibility criteria. If eligible, the individual will be invited to attend an interview session with a diagnostic clinician to confirm the inclusion criteria.

The inclusion criteria for subjects are as follows:
18 to < 35 years of ageDiagnosis of a bipolar disorder I or II (DSM-V criteria)At least one previous episode in the last 2 yearsA minimum of 4 weeks of stable remission since the last affective episode (as measured by the Quick Inventory of Depressive Symptomatology–Clinician Version [QIDS-C] and Young Mania Rating Scale [YMRS], with remission operationalized as QIDS-C < 10 and YMRS < 12)In psychiatric care with a personalized medication plan

The exclusion criteria include the following:
Acute suicidalityDiagnosis of schizoaffective and/or schizophrenic disorder, substance use disorder (last 6 months), antisocial personality disorder, or a predominant borderline personality disorderCurrently (or within the last 6 months) undergoing individual psychotherapy.Intellectual disability (IQ screening whereby MWT-B < 85)A lack of informed consentRefusal of psychiatric care including a personalized medication plan (e.g., with mood-stabilizing medication)

All patients continue to receive their routine psychiatric treatment throughout the study, therefore any necessary changes in medication and patient monitoring will occur as appropriate. Patients’ routine psychiatric care continues to be provided within the community, i.e., separate to the study. In some but not all cases, patients also receive care at the host university hospital.

